### Outcomes

The primary trial endpoint is a composite outcome of microbiologically confirmed incident TB and all-cause mortality, measured as time to first diagnosis of incident TB or death from any cause. Microbiologically confirmed incident TB is defined as active TB diagnosed by either culture, one non-trace positive Xpert Ultra result or two trace-positive Xpert Ultra results, or positive urine LAM result from 3 months after randomization to the end of follow-up (at 2 years, or at the time of last contact for participants who are lost to follow-up). To assess active TB status at the end of follow-up, 2 spot sputum specimens will be collected from all participants who have not taken anti-TB treatment during the study at the final (24 months) study visit for sputum Xpert Ultra testing, liquid culture, and drug susceptibility testing (for participants who received any TPT). Secondary outcomes are presented in Table 2.

**Table 2 Tab2:** Secondary outcomes of the TB SCRIPT trial

Outcome	Numerator	Denominator

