**A. TB incidence**		
Number diagnosed with microbiologically confirmed incident TB within 2 years	# diagnosed with incident TB (incident TB = positive non-trace Xpert Ultra result, two trace Xpert Ultra results, or ≥ 1 positive culture result > 3 months after study entry)	None
2-year incidence of microbiologically confirmed TB	# diagnosed with incident TB	# randomized to corresponding study arm - # treated for prevalent TB (prevalent TB = active TB diagnosed ≤3 months of study entry)
Time to microbiologically confirmed incident TB diagnosis	Days from 3 months post-enrollment to incident TB diagnosis (or censoring)	
Incident rate of microbiologically confirmed TB	# diagnosed with incident TB	(# randomized to corresponding study arm - # treated for prevalent TB)/time in person-years
Number diagnosed with drug-resistant incident TB within 2 years	# diagnosed with incident drug-resistant TB (drug-resistant TB = DST-detected resistance to drugs administered for TPT [e.g., isoniazid])	None
2-year incidence of drug-resistant TB among people receiving TPT	# diagnosed with incident drug-resistant TB	# received TPT of any duration

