### Sample size

The sample size calculations are primarily based on the primary objective (which requires a larger sample size). We expect 2-year mortality of 5.2% and 2-year TB incidence of 7.3% in the control arm [4, 28]. Assuming a two-sided alpha of 0.05 and 12% lost to follow-up, a sample size of 860 participants per arm (1720 total) will provide 80% power to detect a relative reduction of 35% in the 2-year combined outcome (from 12.5% [*n* = 95] to 8.1% [*n* = 62]). This sample size will also provide 85% and 90% power if 2-year mortality is 6.8% and 8.8%, respectively (Table 3). This sample size also gives 80% power to detect a smaller 29% relative reduction if the 2-year combined TB incidence and mortality in the control arm is as high as 17.5% with a 10% loss to follow-up. We will analyze the primary outcome as time-to-event and therefore expect this study power assuming binary outcomes will be a lower bound for study power.

**Table 3 Tab3:** Power calculations (power to detect 35% difference in the combined 2-year TB incidence and mortality outcome when 2-year TB incidence is 7.3%)

2-year mortality		Power
POC CRP-based screening	Symptom-based screening	
3.4%	5.2%	0.80
4.4%	6.8%	0.85
5.1%	7.9%	0.88
5.7%	8.8%	0.90

For the secondary objective, based on published estimates of specificity from similar settings, we estimate no more than 15% of all patients in the control arm will initiate 3HP (and 13.5%, or 90% of all control patients initiating 3HP, will complete 3HP) [16, 17, 20]. This sample size will give more than 90% power to show improvements in the proportion of all patients initiating 3HP by an absolute difference of 6% of more, which is much less than what is considered clinically important; we anticipate 55% of all patients in the POC CRP will initiate 3HP (and 55% of all patients will complete 3HP).

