#### Final TB status assessment

For all participants who have not taken anti-TB treatment during follow-up, we will collect 2 spot sputum specimens at the final (24 months) study visit for sputum Xpert Ultra testing; repeat Xpert Ultra testing, if the initial test is trace-positive; and liquid culture and drug susceptibility testing (DST). Speciation testing will be performed on all positive cultures to confirm the presence of *M. tuberculosis* complex using Ziehl-Neelsen smear microscopy for detection of acid-fast bacilli and SD MPT64 (Standard Diagnostics Bioline TB Ag MPT64, South Korea) for rapid *M. tuberculosis* antigen detection. DST will include susceptibility testing to all first-line TB medications including isoniazid and rifamycin-based drugs. Participants will be classified as having incident TB if at least one of the following criteria are met: at least one sputum culture positive for *M. tuberculosis* complex, one non-trace-positive Xpert Ultra result, or two trace-positive Xpert Ultra results.

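### The rate of drug-resistant TB among TPT recipients has a numerator not limited to recipients, and the protocol conflicts on who gets DST, so either this rate or the arm-wide count can mislead

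*Protocol article*

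**What the plan says.** Section A of Table 2 has two consecutive rows on resistance. The first is an arm-wide count with no denominator: "diagnosed with incident drug-resistant TB (drug-resistant TB = DST-detected resistance to drugs administered for TPT [e.g., isoniazid". The second reads, with label, numerator and denominator in turn, "2-year incidence of drug-resistant TB among people receiving TPT # diagnosed with incident drug-resistant TB # received TPT of any duration". Its numerator cell repeats the count from the first row without a restriction, and its denominator is "received TPT of any duration".

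The protocol describes month-24 DST in two ways. The Outcomes section, which introduces Table 2, limits it: "drug susceptibility testing (for participants who received any TPT". The Final TB status assessment section sets no such limit. It begins "For all participants who have not taken anti-TB treatment during follow-up, we will collect 2 spot sputum specimens at the final (24 months) study visit" and goes on to culture and DST, adding that "DST will include susceptibility testing to all first-line TB medications including isoniazid and rifamycin-based drugs". The Trial design section and Table 1 also list month-24 DST without a TPT condition.

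The Statistical methods section names isoniazid-resistant TB incidence over two years as a secondary outcome, to be analysed in a similar way to the intention-to-treat primary outcome. On uptake, the Sample size section says "we estimate no more than 15% of all patients in the control arm will initiate 3HP" and expects 55% in the CRP arm.

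**The concern.** A rate is interpretable only if everyone who can enter the numerator is also in the denominator. Read cell by cell, this row breaks that rule: a participant who never took TPT and has transmitted resistant TB counts as a case but not as a person at risk. The resulting inflation depends on uptake, and uptake is what the intervention is meant to change, so the distortion would differ by arm and would flatter the arm that gives more TPT.

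The outcome matters because the section on risks to participants names acquired resistance in prevalent cases started on 3HP as a hazard. Whether the distortion occurs depends on who is tested, and there the protocol contradicts itself. The row also does not follow the Statistical methods section, whose approach keeps all randomized participants.

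**Working it through.** **Inputs.** 860 per arm and 3HP uptake of 15% (control, stated as a maximum) and 55% (CRP), all from the Sample size section. The protocol gives no figure for the resistance outcome. The 860 itself checks: 860 × 0.88 = 756.8 evaluable per arm, 12.5% versus 8.125%, two-sided 0.05, gives power 0.7997 against the stated 80%.

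**Notation.** u = TPT uptake; q = two-year risk of resistant incident TB without TPT; kq = the risk with TPT, taken as the same in both arms. For illustration q = 0.7%, about 10% of the planned 7.3% TB incidence. That share is an assumption. The ratios below do not depend on q.

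**1. Denominators.** Control 0.15 × 860 = 129; CRP 0.55 × 860 = 473; 473/129 = 3.67.

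**2. Literal numerator, DST regardless of TPT.** Row value = q[(1 − u) + uk]/u.
- No TPT effect (k = 1): q/0.15 = 6.67q and q/0.55 = 1.82q, ratio 0.27. With q = 0.7% there are 6.0 cases in each arm, and the row shows 4.7% versus 1.3%, although the risk in recipients is 0.7% in both.
- TPT triples the risk (k = 3, assumed): 1.30q/0.15 = 8.67q and 2.10q/0.55 = 3.82q, ratio 0.44. Cases are 7.8 control and 12.6 CRP, yet the row shows 6.1% versus 2.7%.
- In counts: 5 control and 10 CRP cases read as 5/129 = 3.88% versus 10/473 = 2.11%, while the risks over all randomized are 0.58% and 1.16%. CRP would need about 3.67 times the control cases for the row to look equal.

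**3. Clinician-initiated TPT.** The denominator counts any TPT, so uptake may exceed the 3HP figures. If clinicians start TPT in a share c of the rest, u = u₀ + c(1 − u₀).
- c = 0.2: u = 0.32 and 0.64, ratio 0.50 (k = 1) or 0.70 (k = 3).
- c = 0.4: u = 0.49 and 0.73, ratio 0.67 or 0.83.

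**4. DST only in TPT recipients.** Non-recipients cannot be found resistant by month-24 study testing, so the row becomes kq in both arms, ratio 1. The arm-wide count becomes 860·u·kq, with ratio 0.55/0.15 = 3.67 whatever k is. With q = 0.7% and k = 1 it shows 0.9 versus 3.3 cases, where the true numbers are 6.0 in each arm. At c = 0.2 and 0.4 the ratio is 0.64/0.32 = 2.0 and 0.73/0.49 = 1.5.

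**5. All randomized as denominator, DST regardless of TPT.** k = 1: 6.0/860 = 0.70% in both arms. k = 3: 7.8/860 = 0.91% versus 12.6/860 = 1.47%. Both have the right direction.

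**The case against.** The strongest reply is that the row label already confines the outcome to TPT recipients, and that Table 2 is terse elsewhere. The TB incidence row also repeats an unrestricted case count, and the matching exclusion of prevalent cases from incident TB appears only under Statistical methods. The Outcomes section then limits DST to those who received TPT. On that reading numerator and denominator nearly coincide, and only resistant cases in non-recipients found by DST before month 24 could leak in. The protocol does not say whether such testing is done. This stands, and it means that the inflation cannot be asserted unconditionally. It does not settle the row, because other rows of Table 2 do write a subset into the numerator when one is meant, and because the Final TB status assessment section contradicts the restriction on DST.

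A reader might also infer that this row is the trial's only comparative measure of resistance, so that false reassurance would go unchecked. The document does not support that. Statistical methods plans an analysis of isoniazid-resistant TB incidence, Table 2 gives the arm-wide count, and acquired resistance is tabulated by arm with the safety data.

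The case numbers are probably high as well. Study DST is described only at month 24, in people not treated for TB, so fewer than six cases per arm may be observed. That affects precision, not the ratios.

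**Conclusion.** The outcome definition is defective as written, and the size of the harm is conditional. With the numerator read literally and DST done regardless of TPT, equal case counts give a CRP/control ratio of 0.27 at planned uptake, or 0.50 to 0.67 with the assumed clinician-initiated TPT. With DST limited to recipients, the row is close to sound, but the arm-wide count is tilted against CRP by up to 3.67-fold at planned uptake. It would be too strong to conclude that the trial will report falsely low resistance under CRP, because the label and the Outcomes section both point to the benign reading of this row. What the document does support is that it leaves open who can enter the numerator, that each reading distorts one of the two resistance measures, and that the row departs from the approach in Statistical methods. The figures rest on the protocol's 15% and 55% uptake and on resistance risks that do not differ by arm within recipients or within non-recipients.

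**What to change.** 1. Restrict the numerator of this row to TPT recipients diagnosed with incident drug-resistant TB after they started TPT. Label the rate descriptive, because recipients are a post-randomization group selected differently in each arm.
2. Base the between-arm comparison on all incident drug-resistant TB over all participants randomized to the arm, in line with Statistical methods.
3. Reconcile the Outcomes and Final TB status assessment sections on who gets DST. The randomized comparison in item 2 is valid only if testing does not depend on TPT receipt.

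The cost is the wording of one table row, one extra tabulation and one reconciled sentence. If the Outcomes section reflects current practice, some additional DST may be needed. The recipient-only rate will rest on very few cases and should be reported with that caution.

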**B. Mortality**		
Number who died from any cause within 2 years	# deaths from any cause	None
2-year all-cause mortality	# deaths from any cause	# randomized to corresponding study arm
Time to death from any cause	Days from enrollment to death from any cause	
All-cause mortality rate	# deaths from any cause	# randomized to corresponding study arm/time in person-years
Number who died from TB within 2 years	# deaths from confirmed TB + # deaths from probable TB (probable TB = review of medical records suggests TB strongly suspected)	None
2-year TB-specific mortality	# deaths from confirmed TB + # deaths from probable TB	# randomized to corresponding study arm

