### Statistical methods

#### Primary and secondary outcomes

The primary trial outcome is a 2-year composite endpoint of microbiologically confirmed incident TB and all-cause mortality, measured as time to first diagnosis of incident TB or death from any cause. The primary analysis will be by intention-to-treat (ITT), including all participants randomized without regard to the results of baseline TB screening, and we will use a two-sided alpha (0.05 significance) in assessing the effect of the intervention on the primary outcome. Participants with prevalent TB will be included in the analysis to preserve the randomized groups (the ITT principle) but excluded from the outcome of incident TB because subsequent disease is more likely to represent relapse or failure (and these participants will not routinely receive TPT). Time from randomization to first event (diagnosis of incident TB or death from any cause) will be analyzed using the log rank test and Cox proportional hazards models, adjusted for the study site. If data are missing or a patient is lost to follow-up, a patient’s data will be censored in the analysis at the date of last known contact. We will also use the Mantel-Haenszel method to determine standardized incidence rates and incidence rate differences. Balance at baseline on all known and suspected prognostic factors will be assessed, and if important imbalances are found (e.g., differences in median baseline CD4 count), a sensitivity analysis will be conducted using a Cox model to adjust for these factors. We will also assess the impact of clinician-initiated co-interventions (e.g., clinician-initiated TPT, clinician-initiated TB treatment) on the primary outcome. We will conduct a sensitivity analysis in which these participants are censored as soon as they are initiated on TPT or TB treatment by non-study clinicians. Standard checks for variation by enrollment site will also be planned. Secondary outcomes for the primary objective include the individual primary endpoints (TB incidence and mortality analyzed separately) and 2-year isoniazid-resistant TB incidence and will be analyzed using a similar approach; there will be no adjustment for multiplicity since these are pre-specified secondary outcomes.

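### Table 2 defines the 2-year risks of death, TB death and TB as crude proportions of those randomized, so participants lost without an event count as event-free and the absolute risks read too low

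*Protocol article*

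**What the plan says.** Outcomes, Table 2, part B (Mortality) lists "2-year all-cause mortality" as an outcome and gives the row, numerator and denominator as "2-year all-cause mortality # deaths from any cause # randomized to corresponding study arm". The row for 2-year TB-specific mortality has the same denominator. Part A (TB incidence) lists "2-year incidence of microbiologically confirmed TB" as a separate outcome, with denominator "randomized to corresponding study arm - # treated for prevalent TB". The same table also has time-to-event rows and person-year rates for TB and for all-cause death.

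Statistical methods (Primary and secondary outcomes) says that data of a patient who is lost "will be censored in the analysis at the date of last known contact". It adds that TB incidence and mortality, taken separately, will be analysed in much the same way as the primary endpoint: log rank test, Cox model, and Mantel-Haenszel incidence rates and rate differences.

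Sample size states "We expect 2-year mortality of 5.2% and 2-year TB incidence of 7.3% in the control arm" and continues "Assuming a two-sided alpha of 0.05 and 12% lost to follow-up", with 860 per arm and 95 expected composite events in the control arm.

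**The concern.** A proportion with a fixed denominator has no place for censoring. Someone lost at month 4 without an event contributes a full two years of being alive and TB-free, although nothing is known about months 5 to 24. The three rows are named outcomes, and they are the only absolute 2-year risks that the article defines for TB and death. Log rank and Cox give a test and a hazard ratio, and Mantel-Haenszel gives rates; none of these is a 2-year risk.

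At stake is the accuracy of the absolute risks that readers will quote, and whether they can be compared with the planning rates. TB has an added difficulty. After baseline, the month-24 sputum is the only systematic TB test in the schedule. A participant lost earlier cannot be found positive by it, yet remains in the denominator.

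**Working it through.** **Inputs.** From Sample size: 860 per arm, 12% lost, control-arm 2-year mortality 5.2%, TB incidence 7.3%, composite 12.5%, 35% relative reduction; Table 3 gives 3.4% mortality in the CRP arm. Assumed here: constant event hazard, loss independent of outcome, and several patterns for the timing of loss. Competing death is ignored in the TB figures, and the TB clock is run from entry for simplicity.

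**Step 1: the plan's own figure.** Two-proportion formula, pooled variance, no continuity correction, 12.5% against 0.65 × 12.5% = 8.125%: 758 evaluable per arm, and 758 / 0.88 gives 862 (stated: 860). With 860 × 0.88 = 756.8 evaluable, power is 0.800. The sample size reproduces.

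**Step 2: which denominator the planning rates use.** 756.8 × 0.125 = 94.6, the stated 95 events. So the rates apply to followed participants. The same 95 events over 860 randomized would be 95 / 860 = 11.0%.

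**Step 3: what the crude definition returns.** Let F be the true 2-year risk and d = 0.12.

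- All loss at entry: crude = F × (1 − d).
- All loss at 3 months: crude = (1 − d) × F + d × F(3 months).
- Constant loss hazard: h = −ln(1 − F)/2, L = −ln(1 − d)/2, crude = h/(h + L) × [1 − exp(−2(h + L))].

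Worked case, mortality with constant loss hazard: h = 0.0267, L = 0.0639, so crude = 0.2947 × (1 − 0.948 × 0.88) = 0.2947 × 0.1658 = 4.88%.

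| Timing of loss | Mortality, true 5.2% | TB, true 7.3% | Relative error |
|---|---|---|---|
| Spread over 2 years (constant hazard) | 4.88% | 6.86% | −6% |
| All at 3 months | 4.66% | 6.54% | −10% |
| All at entry | 4.58% | 6.42% | −12% |

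The relative error hardly depends on F, so it applies to TB-specific mortality too, for which no planning rate is given.

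**Step 4: TB found only at month 24.** Let s be the share of TB detectable only by the final sputum; the article does not give it. Cases in that share are seen only in those still followed. With loss otherwise spread over time, crude = (1 − s) × 6.86% + s × 7.3% × 0.88. This gives 6.9% at s = 0, 6.6% at s = 0.5 and 6.4% at s = 1.

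**Step 5: comparison between arms.** With 12% loss in both arms, the mortality ratio stays at 0.654 (3.4% / 5.2%). The difference shrinks from −1.8 points to −1.69 (constant hazard) or −1.58 (all at entry). With an assumed 14% loss in the control arm and 10% in the CRP arm, the crude ratio is 0.668 to 0.684. With those losses reversed it is 0.625 to 0.639. The article gives no loss rates by arm.

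**The case against.** The strongest reply is that the inference is already sound. TB incidence and mortality are to be compared by log rank, Cox and person-time rates with censoring, and Table 2 itself carries time-to-event and rate rows. A raw proportion of those randomized is commonly printed beside such analyses, and the two are different summaries. This stands, and it confines the point to the 2-year proportions.

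A second reply is that an article may leave estimation from censored data to the analysis plan. That would hold if the rows were open, but Table 2 fixes both numerator and denominator.

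A third is size. Under evenly spread loss the error is 0.3 to 0.4 points, against standard errors of about 0.8 points for mortality (√(0.052 × 0.948 / 860)) and 0.9 for TB (√(0.073 × 0.927 / 860)). That is fair, although this error goes in a known direction and does not average out.

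Three stronger readings are tempting and are not supported:

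- A reader might infer that all of the 12% lost count as event-free. They do not: events seen before loss enter the numerator, so a 12% error is the limit and not the expectation.
- A reader might infer that the crude risks feed the planned risk differences. The article plans risk differences with Cochran-Mantel-Haenszel weights only for the TPT and prevalent TB outcomes, and it states a rule that missing means no event only for TPT initiation and completion.
- A reader might infer that the trial will show a spurious difference between arms. That needs markedly unequal loss, for which the article gives no figure. Participants and routine clinic staff are blinded, and the retention measures are the same in both arms.

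**Conclusion.** The point holds for the three 2-year proportions in Table 2 and no further. Taken as written, they understate the absolute risks by about 6% in relative terms if loss is spread over the two years, and by at most 12% if all loss is at entry: 5.2% reads 4.9% to 4.6%, and 7.3% reads 6.9% to 6.4%. For TB the figure moves towards the lower end as more cases are found only at month 24. These sizes rest on 12% loss that is independent of outcome and on a constant event hazard.

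The primary endpoint, the log rank and Cox comparisons and the person-time rates are unaffected. With equal loss the risk ratio is essentially unchanged and the risk difference shrinks slightly. Unequal loss would bias a comparison of the crude proportions in either direction.

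**What to change.** Redefine the three rows as cumulative incidence at 24 months, in line with the censoring rule already stated:

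- All-cause death: Kaplan-Meier.
- TB: Aalen-Johansen with death as the competing event, keeping the population that Table 2 defines.
- TB death: Aalen-Johansen with death from other causes as the competing event.

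State the time origin for each, because Table 2 starts the TB clock 3 months after enrolment and the death clock at enrolment. Set the horizon so that the month-24 sputum results fall inside it. Keep the crude numbers over those randomized, labelled as descriptive, and report loss by arm beside them.

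The cost is a change to a few definitions, with standard software and no new data. The limit of the fix should be stated too: these estimators assume that loss is independent of outcome, so if lost participants die more often, the estimates remain too low.
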